#### Data collection

Data is collected at six time-points over 24 months: T(1) at start, T(2) 3 months after start, T(3) 6 months after start, T(4) 9 months after start (end of treatment), T(5) 12 months after start and T(6) 24 months after start. Parents and teachers are asked to fill out the questionnaires at all six measurements occasions. Questionnaires are sent to their homes, but when necessary researchers will help them filling out the questionnaires by telephone or face-to-face. The DAI interview is administered by telephone at T(2) and T(4) by a trained interviewer. Saliva is collected at T(2), T(3) and T(4) on five consecutive days, three times a day (see Measures). During the saliva collection, foster carers are called everyday to complete the PDR. The Strange Situation Procedure and accompanying VU-AMS measure is scheduled one week before the end of the treatment (see Table 2).

**Table 2 T2:** Research procedure

**Study phase**	**Time-point**	**Time after start**	**Action**
**Recruitment**			Assess for eligibility
			Randomization
			Send information
			Complete informed consent^a^
**Treatment**	T(1)	6 weeks	Questionnaires
	T(2)	3 months	Questionnaires, interview, saliva collection
	T(3)	6 months	Questionnaires, saliva collection
	T(4)	9 months	Questionnaires, interview, saliva collection, observation, autonomic nervous system recording
**Follow-up**	T(5)	12 months	Questionnaires
	T(6)	24 months	Questionnaires

^a^ No consent – child randomized to treatment as usual.

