### Intervention

The TAU is an intensive treatment for foster children from 0 to 18 years, aiming to prevent placement breakdown. TAU comprises a 3-month diagnostic phase and 9-month treatment phase, delivered by a multidisciplinary team (system therapist, developmental psychologist, child psychiatrist and social worker). Outcomes of the diagnostic phase direct the treatment that will be provided, for example, trauma therapy, parent–child interaction therapy, individual therapy, medication or a combination of these. In addition, during the treatment phase, foster carers receive two-weekly coaching from a social worker, to enhance parental skills and to provide the foster carers with support. They also participate in systemic family therapy sessions, together with children and other important family members.

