MTFC-P is an intensive behavior focused program for young foster children (3 to 7 years of age), aiming to decrease children’s problem behavior and increase social behaviors to promote further placement stability. For 9 months, children are placed with therapeutic foster carers. Therapeutic foster carers are highly trained foster carers who work as semi-professionals closely with MTFC-P staff. MTFC-P is delivered through a treatment team approach, by a specially trained MTFC-P team led by a program supervisor. Children receive individual training and weekly therapeutic playgroup from a skill trainer. Therapeutic foster carers participate in weekly group meetings and receive frequent home visits and ongoing support from a foster carer consultant. A family therapist supports important members of the biological family. Children receive behavioral interventions that are based upon Patterson’s theory of coercion with its principles of social learning [27], to stimulate pro-social behavior and diminish behavioral problems. A key notion is that behavioral problems result from reinforcing negative behavior and lack of modeling of positive behavior. To tackle this, MTFC-P makes use of two principal techniques. First, skills trainer and therapeutic foster carers reward positive behavior. Second, therapist and foster carers ignore negative behavior; instead, they offer an alternative or put the child on a short time-out from contact. Therapeutic foster carers are responsible for the continuity of children’s behavioral interventions. To maintain a beneficial treatment setting for children, therapeutic foster carers are therefore encouraged to stay consistent and responsive toward the child. In addition, they receive parental strategies to promote positive behavior and effective non-abusive limit setting for problem behavior [28]. After the initial 9 months, children are transferred to an aftercare setting. Here, the skills trainer continues children’s training and foster parents (or birth parents in case of reunification) receive parenting practices for approximately 3 months. Although the US aftercare setting is an adoptive family or the birth family, in the Netherlands children are then placed in a permanent foster family or the birth family. Adoption of foster children in the Netherlands is rare, as the primary aim of foster care services is reunification with the birth parent. Furthermore, because after MTFC-P children no longer need intensive treatment, it is not intended that children stay with the therapeutic foster carers. These trained foster carers will adopt a new child for 9 months.

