### Sample size calculation

Sample size is calculated based on the DAI (see Measures). The DAI is a dichotomous measure reflecting symptoms of disturbed attachment (1 = not or somewhat present, 2 = definitely present). From cross-sectional data it is known that the prevalence of symptoms of disturbed attachment in comparable populations is approximately 40% [39]. Based on unpublished pilot data, which also suggested 40% of participants would be symptomatic at any time-point in the TAU intervention, we expect that in the present randomized controlled trial (RCT), a 40% level of symptomatic individuals will be maintained until the end of the TAU. Based on Fisher and Kim’s study [24], which reported increased secure attachment behavior (behavior that is incompatible with disturbed attachment) after MTFC-P, we expect a decline of disturbed attachment over the course of the MTFC-P. The aim is to reduce the proportion of children with symptoms of disturbed attachment to 5% at the end of MTFC-P. Including 34 children in both conditions can statistically reveal a difference between conditions with 90% power, using Fisher's exact test with a 0.05 two-sided significance level for analysis. The study was initially planned as a ‘normal’ pre-randomization trial. However, we observed low recruitment of participants because children arrive in a crisis situation and obtaining consent from biological parents was problematic (see below, Randomization). We therefore changed to a pre-randomization with single consent method to allow the birth parents enough time to decide on their participation. Parents of children randomized to MTFC-P who refused consent received TAU after randomization. We expected a 10% cross-over rate. This cross-over rate reduces the efficiency of the trial by 19% and requires a 20% addition to the sample size [52]. We therefore augmented the planned sample size from 34 to 40 per treatment arm (under 90% power) to counter the dilution effects by the cross-overs in the intention-to-treat analysis and to diminish the type II error probability.

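### Month 9 is called the end of treatment for both arms, but treatment as usual as described runs 12 months, so outcomes last measured at month 9 cannot support an end-of-treatment conclusion

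*Protocol article*

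**What the plan says.** The timing statements are all in the protocol article.

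- **Data collection** lists "T(4) 9 months after start (end of treatment", for both arms alike. **Table 2** makes T(4) the last visit of the treatment phase and places T(5), at 12 months, under follow-up.
- **Intervention**, on the comparator: "TAU comprises a 3-month diagnostic phase and 9-month treatment phase". The phases are sequential: "Outcomes of the diagnostic phase direct the treatment that will be provided".
- **Intervention**, on MTFC-P: "For 9 months, children are placed with therapeutic foster carers". Children then move to an aftercare family, where the skills trainer continues and the new carers "receive parenting practices for approximately 3 months".
- **Data collection**, on the outcome used for sizing: "The DAI interview is administered by telephone at T(2) and T(4) by a trained interviewer". Saliva, with the Parent Daily Report (PDR) alongside it, is collected at T(2), T(3) and T(4). The Strange Situation with autonomic nervous system (ANS) recording "is scheduled one week before the end of the treatment", and Table 2 places it at T(4). Questionnaires are completed at all six time-points, up to 24 months.
- **Sample size calculation** assumes that "a 40% level of symptomatic individuals will be maintained until the end of the TAU", against 5% at the end of MTFC-P. It adds that pilot data pointed to 40% in TAU whenever measured.
- **Background** words the ANS hypothesis for the end of treatment.

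**The concern.** One label is attached to a visit at which the two arms are at different stages. The MTFC-P arm has just finished its therapeutic placement, and only aftercare remains. The TAU arm, as described, is still in its main treatment phase. For outcomes measured again later this would be a minor matter of naming. The DAI, cortisol, PDR, Strange Situation and ANS measures are not measured again, so T(4) supplies their final comparison.

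If the results are reported as an end-of-treatment comparison, readers will take it that both programmes had been delivered. On the description given, no DAI, Strange Situation or ANS measurement is made at the end of TAU. The sample-size premise and the ANS hypothesis are nevertheless worded for that point.

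**Working it through.** **Step 1. Durations (inputs: Intervention section).**

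| | TAU | MTFC-P |
|---|---|---|
| First phase | 3 months, diagnosis | 9 months, therapeutic placement |
| Second phase | 9 months, treatment | about 3 months, aftercare |
| Total | 3 + 9 = 12 months | 9 + 3 = about 12 months |
| Delivered at month 9 | diagnosis, plus 9 − 3 = 6 of 9 treatment months (67%) | whole placement (9 of 9 months) |
| Outstanding at month 9 | 9 − 6 = 3 treatment months | about 3 months of aftercare |

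Both programmes are thus at 9 of about 12 months (75%) in elapsed time, but in different phases. The label is imprecise for both arms. Only TAU is still in its main treatment phase.

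**Step 2. Which outcomes depend on T(4) (inputs: Data collection, Table 2).**

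| Outcome | Measured at | Later measurement |
|---|---|---|
| DAI | months 3 and 9 | none |
| Cortisol, PDR | months 3, 6 and 9 | none |
| Strange Situation, ANS | month 9 | none |
| Questionnaires (carer and teacher) | all six time-points | months 12 and 24 |

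The labelling conflict therefore bears mainly on the first three rows.

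**Step 3. Does the sample size depend on the label?** The inputs from Sample size calculation are 40% against 5%, two-sided 0.05, 90% power, Fisher's exact test, 34 per arm, 10% cross-over and 40 per arm after inflation.

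- Mean proportion: (0.40 + 0.05)/2 = 0.225. Uncorrected n = [1.96·√(2·0.225·0.775) + 1.2816·√(0.40·0.60 + 0.05·0.95)]² / 0.35² = 27.8, so 28 per arm.
- Continuity correction: (n/4)·[1 + √(1 + 4/(n·0.35))]² with n = 27.8 gives 33.2, so 34 per arm. This is the stated figure.
- Exact enumeration of the two-sided Fisher test at 34 per arm gives power 0.937.
- With 10% cross-over the MTFC-P rate becomes 0.9·0.05 + 0.1·0.40 = 0.085. Exact power at 40 per arm is then 0.900.

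The arithmetic reproduces. A TAU rate held at 40% up to the end of TAU includes month 9, and the pilot statement covers any time-point. The premise therefore already applies at T(4), although it is worded for a point at which no DAI is taken.

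The document gives no separate month-9 TAU rate. For an assumed range at 40 per arm, with 5% on MTFC-P and 10% of that arm crossing over to the TAU rate, exact power is:

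| TAU rate at month 9 | 30% | 35% | 40% | 45% | 50% |
|---|---|---|---|---|---|
| Power | 0.68 | 0.81 | 0.90 | 0.95 | 0.98 |

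This shows sensitivity to the rate. It is not evidence that the rate at month 9 differs from 40%.

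**Step 4. Is the start date clear?** Data collection counts visits from the start. The cortisol section counts them from the start of treatment. TAU has a named treatment phase that begins at month 3, so the zero point should be stated. The text favours one common clock: Randomization says allocation shares vary so that treatment is immediate, and Discussion links the start of the intervention to the child being new in the foster family.

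**The case against.** The strongest reply is that each programme lasts about 12 months and each is at month 9 at T(4). A comparison at equal time from start is a legitimate randomized comparison of two care strategies. Table 2 fixes one visit date for everyone, and the questionnaires run on to 24 months. All of this stands, and it reduces the matter to what the T(4) visit may be called and what may be concluded from it. It does not remove the conflict between the label and the described length of TAU.

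Three stronger readings are tempting, and the document does not support them.

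- *A reader might infer that the T(4) contrast is biased in favour of MTFC-P because TAU is unfinished.* That requires the last months of TAU to add benefit. The document gives no TAU trajectory, and for disturbed attachment its own premise is a flat 40%, under which the timing adds nothing. MTFC-P also has a component outstanding. A figure in standard deviation units would need an assumed TAU effect and an assumed pattern of accrual, and the document contains neither.
- *A reader might infer that the sample size is undermined.* It is not: the stated figure reproduces and the 40% premise covers month 9.
- *A reader might infer that TAU runs on a second clock starting after diagnosis, or that the Strange Situation has two dates.* Nothing says so. Randomization and Discussion point to a common start, and Table 2 puts the observation at T(4) for both arms.

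**Conclusion.** The contradiction is in the text and should be corrected. At T(4) the MTFC-P placement is complete, while TAU as described has 3 of its 9 treatment-phase months left. Conclusions on the DAI, Strange Situation, ANS, cortisol and PDR can be stated as a 9-month comparison. They cannot be stated as an end-of-treatment comparison for TAU.

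This rests on two assumptions: that the TAU phases run one after the other, as the Intervention section implies, and that the start means entry to the programme in both arms. The size and direction of any effect on the estimates cannot be derived from the document. The randomized comparison at month 9 remains valid, and no change in sample size follows.

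**What to change.** 1. Reconcile the ANS hypothesis in Background, the two programme descriptions in Intervention, the premise in Sample size calculation, Data collection and Table 2. If the TAU duration is not meant as it reads, the Intervention section should say so. No programme length is recommended here.
2. Define the start as one common date for both arms and time every visit, including the Strange Situation and ANS recording, from it.
3. Relabel T(4) as 9 months after start, and word the sample-size premise and the ANS hypothesis to match.
4. Limit DAI, Strange Situation, ANS, cortisol and PDR conclusions to a 9-month comparison, stating that part of TAU and the MTFC-P aftercare were still to be completed.
5. Rest any statement about completed programmes only on questionnaires at T(5) or later, with a caveat. By then MTFC-P children have left the therapeutic carers, so both the carer informant and the placement have changed in that arm. The Discussion itself warns that a new placement can shift problems temporarily. The teacher form is less exposed to this, provided that teachers or daycare providers do complete it. Its description under Measures names foster parents in one sentence and teachers or daycare providers in another.

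The cost is wording only, with no new data and no change to numbers or treatment. Inclusion was still in progress according to Status of the trial, so the change could be made before reporting. The downside is that the attachment claim becomes one about 9 months after start and no longer one about the end of treatment.

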#### Blinding

Researchers coding the interviews and observations are blind to group allocation. The condition is disclosed to participants immediately after referral.

#### Planned statistical analyses

Analyses are performed using the software package SPSS (Statistical Package for the Social Sciences), version 17.0. Fisher’s exact tests are used for the categorical data, effect sizes are estimated by the relative risks, absolute risks and relative risk reduction. Effect parameters are presented within a 95% confidence interval. The continuous measures are analyzed with repeated measures (mixed models) and independent t-tests. Effect sizes are indicated by partial eta squared and Cohen’s d. Primary analyses are performed following the intention-to-treat principle. However, we will also perform a ‘treatment received’ analysis and a separate comparison of children whose parents refused participation and who received TAU after randomization to MTFC-P. Depending on the amount and type of data missing we will explore possibilities to deal with missing data, but we plan to use mixed models.

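### The one missing-data method named in the plan does not reach the DAI at T(4), the outcome that sizes the trial, so its Fisher's exact test as written uses only children with a T(4) interview

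*Protocol article*

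**What the plan says.** All places are in the protocol article.

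- **Sizing outcome** (Sample size calculation): "Sample size is calculated based on the DAI (see Measures). The DAI is a dichotomous measure reflecting symptoms of disturbed attachment". The assumptions are that "a 40% level of symptomatic individuals will be maintained until the end of the TAU" and that the aim is to "reduce the proportion of children with symptoms of disturbed attachment to 5% at the end of MTFC-P". The test is a two-sided Fisher's exact test at 0.05, and "Including 34 children in both conditions can statistically reveal a difference between conditions with 90% power". The number is then raised to 40 per arm for an expected 10% cross-over. No other reason for the increase is given.
- **Timing** (Data collection): "The DAI interview is administered by telephone at T(2) and T(4) by a trained interviewer", that is, at 3 and 9 months. Questionnaires are collected at all six time-points.
- **Analysis** (Planned statistical analyses): Fisher's "exact tests are used for the categorical data". Continuous measures get repeated-measures mixed models and t-tests. The primary analyses follow intention to treat.
- **Missing data** (same section): depending on how much is missing and of what type, "we will explore possibilities to deal with missing data, but we plan to use mixed models".

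**The concern.** The section fixes three things that do not fit together for the DAI: the test, the type of outcome that each method serves, and the method for missing data. A mixed model on continuous scales keeps a child who misses one visit, because that child's other visits still contribute. A two-by-two table of the T(4) DAI cannot do this. A child without a T(4) interview has no cell, and a T(2) DAI already held for that child plays no part.

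Two things are at stake. The first is power, because the enlarged sample has no allowance for missing interviews. The second is bias, if children without a T(4) interview differ in symptom status from those with one. The Background section ties behavioural and relationship problems to placement breakdown, and the DAI is a telephone interview, so loss related to severity is plausible.

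**Working it through.** **Inputs.** From Sample size calculation: TAU rate 0.40, MTFC-P rate 0.05, two-sided alpha 0.05, power 90%, 34 per arm raised to 40, cross-over 10%. The proportion of missing T(4) interviews is not given, so 0 to 30% is assumed.

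**1. The plan's own figure.** Mean rate (0.40 + 0.05)/2 = 0.225; difference d = 0.35.

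Without continuity correction, n = [1.96·√(2·0.225·0.775) + 1.2816·√(0.40·0.60 + 0.05·0.95)]² / 0.35² = (1.1575 + 0.6872)² / 0.1225 = 27.8, so 28.

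With continuity correction, n = (27.8/4)·[1 + √(1 + 4/(27.8·0.35))]² = 33.2, so 34.

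The stated 34 is reproduced. Exact Fisher power at 34 per arm, by enumerating every two-by-two table, is 0.937.

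**2. Rates after cross-over.** By intention to treat, the MTFC-P rate becomes 0.9 × 0.05 + 0.1 × 0.40 = 0.085. At 40 per arm, exact Fisher power for 0.40 v 0.085 is 0.900. This agrees with the stated 90%, provided that every child has a T(4) DAI.

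**3. Missing T(4) interviews, unrelated to symptoms (assumed rates).** Number analysed per arm = 40 × (1 − proportion missing).

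| Missing | Per arm | Fisher power, 40% v 8.5% |
|---|---|---|
| 0% | 40 | 0.900 |
| 5% | 38 | 0.880 |
| 10% | 36 | 0.856 |
| 15% | 34 | 0.828 |
| 20% | 32 | 0.807 |
| 30% | 28 | 0.723 |

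**4. Loss that depends on T(4) status (illustration only).** Assume that 25% of symptomatic and 5% of non-symptomatic children are missing.

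- TAU observed rate: 0.40·0.75 / (0.40·0.75 + 0.60·0.95) = 0.300/0.870 = 0.345, on 40 × 0.870 ≈ 35 children.
- MTFC-P observed rate: 0.085·0.75 / (0.085·0.75 + 0.915·0.95) = 0.0638/0.9330 = 0.068, on 40 × 0.933 ≈ 37 children.
- Loss in both arms: the risk difference falls from 31.5 to about 27.6 points, and Fisher power is about 0.84.
- Loss in TAU only: 34.5% v 8.5% on 35 v 40 children, and power is about 0.76.

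**5. Choice of exact test.** At 40 per arm, Fisher's test has a true size of at most 0.033. Boschloo's test has a size of 0.048, so still below 0.05, and power 0.925 against 0.900. At 36 per arm the powers are 0.907 and 0.856.

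**6. Expected events.** MTFC-P: 40 × 0.085 = 3.4. TAU: 40 × 0.40 = 16. The chance of no event in MTFC-P is 0.915⁴⁰ ≈ 0.03, or 0.95⁴⁰ ≈ 0.13 at the 5% target.

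**The case against.** **The article does not say that children are dropped.** A reader might infer that the plan adopts a complete-case analysis. It does not say so. Intention to treat is declared, and the missing-data sentence leaves other options open. This stands as a limit on the claim. What remains is that the one concrete method is tied to continuous measures, and the alternatives are to be chosen according to the missing data that arise.

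**A journal article may leave missing-data detail to a fuller document.** True in general. Here, though, the article itself names the tests, their outcome types and a missing-data method, and for the sizing outcome these do not meet.

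**Loss through placement breakdown is conjecture.** A reader might infer that the most disturbed children will be lost, and mostly from TAU. Nothing in the article says that breakdown ends follow-up or that a new carer cannot be interviewed. The 25% and 5% in step 4 are invented for illustration. With loss in both arms, the relative risk moves only from 0.085/0.40 = 0.2125 to about 0.198, and the odds ratio stays at 0.139. With loss in TAU only, the bias is towards no effect.

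**The usual remedies would not fully repair such loss.** Correct. In step 4 the loss depends on the unseen T(4) status, whereas imputation assumes missing at random. It helps only as far as the T(2) DAI and the other scores predict the T(4) result, and the article gives no correlation from which to judge that. With 3.4 expected events in MTFC-P, a random-effects logistic model with arm by time could also fail to converge.

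**Fisher's test is a defensible choice.** It is. Design and analysis agree, and the 90% is right for that test. A reader might take the low true size as a flaw in the power calculation; step 2 shows that it is not.

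**Conclusion.** The point holds in a limited form. The named missing-data method does not cover the comparison that sizes the trial, and that comparison, carried out as written, rests on children with a T(4) interview only, contrary to the intention-to-treat statement. The sample size itself is reproduced and is not wrong.

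The cost in power is moderate: from 0.900 to between 0.856 and 0.807 if 10 to 20% of interviews are missing unrelated to symptoms. This rests on the plan's 40% and 5% rates, one-way cross-over of 10%, equal loss in both arms and missing rates that are assumed. The documents support no figure for bias, and neither its presence nor its direction can be claimed. It is a change that should be made, and the data for it are already being collected.

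**What to change.** 1. Prespecify that the T(4) DAI comparison includes all randomised children with study data, analysed as randomised, with missing T(4) DAI values multiply imputed from arm, T(2) DAI, age and the questionnaire scores. Use few summary scores in the imputation model, because only about 16 + 3.4 = 19.4 events are expected.
2. Keep the two-by-two exact test as the complete-case analysis and label it so.
3. Add a sensitivity analysis in which the chance of a missing interview depends on T(4) status, varied separately by arm, because imputation removes such bias only in part.
4. Optional: replace Fisher's test with Boschloo's in the complete-case analysis (0.925 v 0.900 at 40 per arm). This gains efficiency and corrects no error.

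A random-effects logistic model on T(2) and T(4) is not recommended as the main remedy, given so few events.

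**Cost.** A few sentences of text, some programming, and reliance on the missing-at-random assumption in the main result. Boschloo's test may need software other than the SPSS version named. No new data are needed, and inclusion was still in progress when the article was published, so the change can be made before the results are seen.

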Including sufficient participants using random allocation is a major challenge in this study. Following conventional randomization we do not expect researchers to be able to ensure that the child’s legal authority signs informed consent before the child must be allocated to a treatment [53]. Referral to foster care is often made in crisis and immediate start of care is a prerequisite. Concurrently, start of foster care is usually accompanied with resistance or absence of the biological parent (the child’s legal authority) or a vacuum in authority. We expect that this brief time interval between referral and start of the intervention together with inaccessibility of a legal authority will hamper random allocations and causes preliminary loss of participants. A pre-randomization trial, wherein randomization is determined prior to informed consent, is implemented as we expect this design to promote random allocation and improve inclusion of participants [55] as it extents the time period between referral and start of the treatment. Researchers therefore have more time to obtain informed consent, avoiding preliminary dropout. However, there is a serious statistical drawback to using pre-randomization according to Zelen, through participant crossover to TAU [52,54]. Crossover would also occur in a normal post-randomization RCT but is likely to be greater in the Zelen design because participants that refuse one of the treatments of interest would be excluded from participation in a normal RCT. These crossovers introduce dilution bias that will lead to an underestimate of the ‘true’ treatment effect in the intention-to-treat analysis. To cope with this dilution effect, we increased the sample size correspondingly to reduce the likelihood of a type II error. Advantages of the Zelen design are that it is closer to normal clinical practice because the allocated treatment is discussed with the parent who may or may not refuse the treatment on offer. This also results in a more representative sample of participants because, within a usual RCT, refusal of consent usually leads to a trial sample that is different from the general treated population. We therefore will also perform a ‘treatment received’ analysis in addition to the planned intention-to-treat analysis to represent the more natural state of affairs that results from pre-randomization.

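### The treatment-received and refuser comparisons group children by parental refusal while the ITT estimate stays diluted; a complier-average effect should be added and both comparisons labelled descriptive

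*Protocol article*

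**What the plan says.** The Planned statistical analyses section makes ITT primary. It then commits to a treatment-received analysis and to "a separate comparison of children whose parents refused participation and who received TAU after randomization to MTFC-P". The group with which these children are to be compared is not named.

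The Discussion says of ITT: "These crossovers introduce dilution bias that will lead to an underestimate" of the treatment effect. Its stated answer to dilution is the larger sample. The treatment-received analysis is given another purpose; it is an "analysis in addition to the planned intention-to-treat analysis to represent the more natural state of affairs that results from pre-randomization".

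The Sample size calculation section gives the figures: "We expected a 10% cross-over rate", with 34 per arm raised to 40. Cross-over runs one way only, since families who refuse after allocation to MTFC-P receive TAU. That section counts these children within the ITT analysis. The Exclusion criteria section, however, removes from the randomised trial children whose legal authorities do not consent or whose foster parents disagree with the assigned treatment. The Randomization section adds that the allocation ratio changes about every six months with available places.

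**The concern.** The protocol recognises that ITT will be diluted, but none of its planned analyses estimates the effect of receiving MTFC-P from the randomised contrast. The treatment-received analysis moves MTFC-P refusers into the TAU group and leaves only acceptors in the MTFC-P group. If refusers differ in prognosis, this contrast shows a difference even when MTFC-P does nothing. Refusers can be identified only in the MTFC-P arm, because in the TAU arm the same families would receive TAU anyway. The refuser comparison therefore has no randomised counterpart.

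The stated purpose does not rescue the treatment-received analysis. If the natural state of affairs is one in which a parent may decline the treatment on offer, the effect of offering MTFC-P, refusals included, is what ITT already estimates. The risk is that a treatment-received result larger than ITT is read as the undiluted effect when part of it is selection.

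**Working it through.** All differences are TAU minus MTFC-P, so positive values favour MTFC-P.

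**Inputs (Sample size calculation section)**
- TAU risk 40%: "a 40% level of symptomatic individuals will be maintained until the end of the TAU".
- MTFC-P risk 5%: the aim is to "reduce the proportion of children with symptoms of disturbed attachment to 5% at the end of MTFC-P".
- Fisher's exact test "with a 0.05 two-sided significance level for analysis".
- Power and base size: "Including 34 children in both conditions can statistically reveal a difference between conditions with 90% power".
- Cross-over 10%, MTFC-P to TAU only; 40 per arm after inflation.

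**1. The plan's figures reproduce.** The continuity-corrected two-proportion formula for 40% against 5% at 90% power gives 34 per arm (28 without the correction). Exact Fisher power at 34 per arm is 93.7%. The efficiency loss is 1 − 0.9² = 19%. Inflation gives 34 × 1.2 = 40.8 or 34 / 0.81 = 42.0, close to the planned 40. The diluted MTFC-P risk is 0.9 × 5% + 0.1 × 40% = 8.5%, and exact Fisher power for 40% against 8.5% at 40 per arm is 90.0%. The inflation does what it is meant to do for power.

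**2. The estimate stays diluted.** ITT difference = 40 − 8.5 = 31.5 points. SE = √(0.40 × 0.60/40 + 0.085 × 0.915/40) = 8.9 points; 95% CI 14.0 to 49.0. The planned effect of treatment is 40 − 5 = 35 points.

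**3. Treatment-received difference when MTFC-P has no effect.** Let c be the refusal share and r the refusers' risk under TAU, with equal arms and the overall risk held at 40%. The values of r are assumptions; the documents give none.
- Acceptors' risk: (0.40 − c·r)/(1 − c)
- Pooled TAU risk (TAU arm plus refusers): (0.40 + c·r)/(1 + c)
- Difference: 2c(r − 0.40)/(1 − c²)

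| r | c = 10% | c = 20% |
|---|---|---|
| 20% | −4.0 points | −8.3 points |
| 40% | 0 | 0 |
| 60% | +4.0 points | +8.3 points |
| 80% | +8.1 points | +16.7 points |

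If MTFC-P does work, the same values are the bias of the treatment-received difference for the effect in acceptors. Under no effect, ITT and the complier-average effect are 0 in every cell.

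**4. Complier-average effect.** This is the ITT difference divided by the share of MTFC-P-allocated children who start MTFC-P. On the plan's inputs it is 31.5/0.9 = 35.0 points, SE 8.9/0.9 = 9.9, 95% CI 15.6 to 54.4, treating the refusal share as known. The z statistic is that of ITT, so the sample size need not change. A case with different prognosis separates the methods. Take c = 10%, r = 80% and MTFC-P risk 5%:
- Acceptors' TAU risk (0.40 − 0.08)/0.9 = 35.6%; true effect in acceptors 30.6 points
- ITT: 40 − (0.9 × 5 + 0.1 × 80) = 27.5; complier-average 27.5/0.9 = 30.6
- Treatment received: (0.40 + 0.08)/1.1 = 43.6%; 43.6 − 5 = 38.6, which is 8.1 too high

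**5. Refuser comparison.** 10% of 40 is about 4 children. If 2 of 4 were symptomatic, the exact 95% interval would run from about 7% to 93%.

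**6. If refusers are excluded instead.** If refusers left the MTFC-P arm only, with r = 80% and no effect, the remaining contrast would be 40 − 35.6 = 4.4 points. Neither ITT nor a complier-average effect built on it would then be protected.

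**The case against.** The strongest reply is that the criticised analyses are supplementary. ITT is primary, and the larger sample is the stated answer to dilution and achieves its purpose. A reader might infer that the treatment-received analysis is the protocol's remedy for dilution, or is offered as the true effect. The Discussion does not say so: it gives that analysis a descriptive role and uses the word true only when describing what ITT underestimates. The refuser comparison, with no comparator named, can likewise be read as a check on selection. All of this stands and limits the point to the supplementary analyses.

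A reader might also take 31.5/0.9 = 35 as proof that the complier-average effect is better. It is not. That example sets refusers' risk at 40%, where the treatment-received difference is 40 − 5 = 35 as well. The methods separate only when refusers' risk differs.

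Nor do the documents show that refusers differ. The Randomization section describes parental resistance or absence for referred children generally. A link to outcome is plausible but assumed. At 10% refusal the bias is modest: with 36 against 44 children and a risk near 40%, the SE is √(0.24/36 + 0.24/44) = 11 points, so 4 to 8 points is under one SE.

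Finally, the complier-average effect is not free of assumptions, and an analysis plan that is not shown may already contain it. What remains is that the protocol itself commits to two comparisons based on refusal and does not give them a descriptive label in its analysis section.

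**Conclusion.** The concern holds for the supplementary analyses, as a moderate point. The primary analysis and the sample size are sound on the plan's figures. The larger sample restores power (90.0%) but leaves the estimate at 31.5 instead of 35 points. The treatment-received contrast is open to selection bias of about 4 to 8 points in absolute size at 10% refusal, and about 8 to 17 at 20%, for refusers' risks of 20%, 60% or 80%. It is zero when their risk is 40%, and its sign depends on who refuses. The refuser comparison carries almost no information.

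These sizes rest on assumed refuser risks, an overall risk of 40% and equal arms. The advantage of the complier-average effect rests on refusers staying in their allocated arm with outcomes, on allocation itself not affecting refusers' outcomes (the exclusion restriction), and on cross-over remaining one-way. The conflict between the Exclusion criteria section and the Sample size calculation and Randomization sections leaves the first condition open.

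**What to change.** - Keep ITT primary.
- Add a complier-average causal effect as the estimate of the effect of receiving MTFC-P: the ITT difference stratified by allocation period, divided by the share of MTFC-P-allocated children who started MTFC-P, with a bootstrap or two-stage least-squares interval. State its assumptions. Stratification is needed because the allocation ratio varies by period.
- Label the treatment-received and refuser results descriptive only, and name the comparator for the refusers.
- Reconcile the Exclusion criteria section with the Sample size calculation and Randomization sections, so that refusers are analysed in their allocated arm with their outcomes. The planned ITT analysis needs this as well.

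The cost is a few lines of analysis and no change in sample size. The interval is somewhat wider than that of the treatment-received analysis. On the plan's figures, the latter has SE √(0.05 × 0.95/36 + 0.40 × 0.60/44) = 8.2 points, against 9.9 for the complier-average effect. The result also depends on the exclusion restriction and on having refusers' outcomes, or a missing-data method for them.
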